## Abstract

**Objective:**

Protocol for randomized controlled trial (RCT) examining effects of novel, remotely delivered intervention (called GetUp&Go) to increase physical activity (PA) in chronic, moderate-severe traumatic brain injury (msTBI), including a mobile health (mHealth) component.

**Design:**

RCT (Clinicaltrials.gov NCT06028334) with 1:1 randomization to 10 weeks of immediate treatment (IT) or waitlist (WL), with primary outcome measured at 10 weeks. A second randomization to 10 weeks of continued mHealth support vs. no treatment will allow for examination of effects of mHealth on maintenance of treatment gains.

**Participants:**

70 community-dwelling adults ≥6 months post msTBI; medically cleared and physically/ cognitively able to participate; physically inactive (≤23 weekly moderate/ vigorous activity units on Godin Leisure-Time Exercise Questionnaire).

**Interventions:**

10-week GetUp&Go program: manualized, remotely delivered intervention with ingredients based on theoretical model of behavior change, in which participants set individual goals and programs for increasing PA; mHealth support via chatbot that delivers personalized messages, reminders, and reinforcement to participant phone.

**Main outcome measures:**

Primary outcome is activity count measured by accelerometer worn on wrist for 7 days at all assessment intervals. Secondary outcomes include emotional function, fatigue, sleep, pain, health-related quality of life.

**Discussion:**

While conclusions await the results of the trial, we consider PA enhancement to be a valuable and under-studied direction for treatment of msTBI. The advantages of the described treatment include strong theoretical and empirical basis for the treatment protocol, which has been designed to help to circumvent difficulties with initiation, persistence, and memory that interfere with the ability to develop healthful habits and routines following msTBI.

## Introduction

1

The importance of physical activity (PA) for human health and well-being is incontrovertible. Widely cited guidelines state that adults aged 18+ should engage weekly in at least 150 min of moderate-to-vigorous PA (MVPA) or 75 min of vigorous-intensity PA, plus ≥2 bouts of strengthening activities involving all major muscle groups (1). PA at this level is associated with many health benefits including lower risk of all-cause mortality, reduced risk of depression and anxiety, improved sleep, and better quality of life (2). In the general population there is also a strong association between PA and emotional well-being (3).

Moderate to severe traumatic brain injury (msTBI) is a significant public health problem. It is estimated that in the US alone, almost 20% of the population has experienced TBI with loss of consciousness (4). Although many TBIs lead to transient symptoms, msTBI can cause potentially lifelong difficulties with physical, cognitive, and emotional function, leading to the recent conceptualization of TBI as a chronic health condition (5). A growing body of research shows that people with msTBI have decreased PA levels after msTBI compared to preinjury (6–8), as well as increased propensity for sedentary behavior and weight gain (9) and significantly elevated risk of cardiovascular disease (10). Among the many barriers to PA reported by those with msTBI are potential for pain, discomfort, or embarrassment; safety concerns; insufficient knowledge about PA or lack of access to PA-friendly spaces; limitations in time, transportation and other resources; fatigue; and poor motivation (11–13).

Despite these barriers, people with msTBI have expressed the view that PA is very important and report a high level of interest in programs promoting PA (12, 14), particularly those adapted to the specific needs of people with brain injury (15). PA programs delivered remotely are also acceptable to this population (16). Studies show that even those with mobility limitations due to msTBI are able to attain cardiovascular fitness equivalent to their uninjured counterparts (17). Several reports suggest that PA also improves cognitive function following msTBI (18, 19). An intriguing observational study (20) revealed that in persons with a history of TBI, there were significantly stronger correlations between PA and self-reported measures of cognitive function and global health, compared to the same correlations in uninjured controls. Although causality cannot be assumed, one implication of this finding is that people with TBI could experience a particularly high degree of health benefit from increased PA.

There is a modest literature describing efforts to increase PA for people with msTBI; most have tested short-term aerobic exercise programs, using a variety of outcome measures. A 2020 systematic review included 9 studies that used reduction in depression symptoms as a primary outcome (21). Small to medium positive effects on mood were noted overall; however, the effects on sustained PA were largely unexamined. Another group of studies examined cardiovascular endurance and/ or resistance training. A 2010 narrative review (22) and a 2017 Cochrane review (23) concluded that exercise training is safe in msTBI and mostly effective in improving fitness, but that the clinical value remained unclear. That is, the impact on metabolic measures of fitness was confirmed, but not the effect of increased PA in daily life or health and well-being. A more flexible approach, using individually tailored PA plans rather than prescribed exercise regimens, has been used by a few investigators. For example, Clanchy and colleagues (24, 25) delivered 10 sessions of PA promotion to persons with msTBI and other forms of acquired brain injury, both in-person and by phone, with the frequency of contact diminishing over time. The program emphasized safe, sustainable, and enjoyable activities, and included individualized relapse-prevention strategies as a final step. Therapist contact was withdrawn so that self-maintained PA could be measured 12 weeks after treatment cessation. While robust effects were found for increased PA after treatment, there was limited maintenance of gains at follow-up (24). The authors emphasized the importance of continued support to maintain gains in PA. Similarly, the most recent systematic review of PA interventions for msTBI (26) echoed the need for follow-up. This review also noted that the majority of studies to date are of poor methodologic quality, limiting conclusions about the impact of PA on function and quality of life in this population. The authors also urged the use of a broader range of outcome measures, including health and participation measures; more attention to study power; and more rigorous study design.

As detailed below, we have attended to all of these recommendations in developing the current trial. We designed an intervention for promoting PA in people with msTBI that has the following characteristics.

### Theoretical basis

1.1

Few efforts to increase PA in this population have been grounded in theory, yet the literature on PA promotion in the general population has yielded rich insights from theoretical models of health-related behavior change. The ingredients used in the current intervention were derived from a highly influential model: the COM-B framework of Michie and colleagues (27). This framework, which has been called a “meta-theory (28),” has been rigorously developed and validated in extensive research on health behavior (29–33) and was strongly supported in a review of major theoretical approaches to PA promotion (34). According to this model, voluntary behavior and changes in behavior are a function of three factors: **C**apability, **O**pportunity, and **M**otivation. Capability refers to both cognitive/ psychological capacity, e.g., knowledge about why and how to perform a desired behavior and remembering to do it, and the physical ability to perform it. Opportunity means access to necessary social and physical/ logistic resources, including space, time, and social support. Motivation refers both to conscious/ reflective factors affecting drive and reward, and reflexive/ automatic motivation (e.g., priming) that may enhance habit formation (27).

### Individual tailoring

1.2

Within this theoretical framework, we designed the intervention to accommodate a wide range of individual choices and physical capabilities. In this regard we were guided by the work of Clanchy et al. (24, 25) as well as research showing a *dose-response* relationship between PA increase and health benefit—meaning that it is not necessary to meet the standard recommendations for PA levels to experience improvements in mood, energy, and quality of life, as well as health risk reduction (35).

### Remote delivery and mobile health support

1.3

Studies have revealed that personalized PA programs can successfully be delivered via remote means including phone, web, and text messages (36, 37). A recent review focused on smartphone-delivered PA promotion for mental health emphasized the importance of including education about the value of PA and personalized coaching within the intervention (38). There is a burgeoning literature showing that persons with msTBI, even those with significant neurocognitive impairment, can successfully engage in, and benefit from, interventions delivered via phone (39–41) and other remote methods. Mobile health (mHealth) interventions, such as smartphone apps and interventions delivered by text, are increasingly being used in TBI rehabilitation and research (42, 43). As described below, the current study provides both remote therapist contact and mHealth support from a chatbot called RehaBot, which was developed in our laboratory specifically for the needs of participants with TBI. In a feasibility study, participants with msTBI found RehaBot both easy to use and enjoyable (44).

### Objective measurement of PA

1.4

There is considerable evidence that self-report measures of PA are less reliable than objective measurement using accelerometers worn on the body (45); the latter method has been shown to be reliable in persons with TBI (46). In this study, our primary outcome is increase in PA from pre- to post-treatment, measured with a wrist-worn accelerometer that has been successfully used with the msTBI population (47).

### Attention to long-term impact

1.5

As described below, we include a follow-through phase to assess the effects of the intervention after therapist support is withdrawn, with randomization either to no continued support, or continued use of RehaBot (without therapist intervention). We also include treatment ingredients that have been shown to help sustain new PA habits, and less sedentary behavior, as part of daily life (36, 48).

### Consumer input

1.6

Throughout intervention development, consumer input was obtained through multiple structured methods. Two paid consumer consultants with lived experience of msTBI and self-reported difficulties with PA were engaged in this process. Input was collected through facilitated focus group sessions where consultants reviewed and provided feedback on the treatment rationale and session structure; visual materials and participant handouts; and the use of RehaBot to deliver just-in-time support for PA in participants' daily environments. Additionally, consumer consultants participated in pilot testing of treatment sessions, providing feedback on feasibility, acceptability, and comprehensibility of intervention components. This iterative feedback was incorporated into the final treatment manual. Consultants also selected the name of the intervention: *GetUp&Go*.

### Aims and hypotheses

1.7

The aim of this study is to examine the efficacy of the GetUp&Go intervention for increasing PA and enhancing associated functional outcomes in msTBI. We propose the following hypotheses:

1a. Participants who receive the GetUp&Go intervention directly after randomization will show significantly more increase in PA, as assessed by average accelerometer activity counts/ day, from pre-randomization baseline to post-treatment 10 weeks later, compared to those waitlisted for 10 weeks.

1b. Participants randomized to immediate treatment (IT) will also show significantly more improvement compared to waitlisted participants (WL) on secondary outcome measures including intensity of PA (derived from accelerometer readings), self-reported PA, emotional function, fatigue, sleep, pain, and health-related quality of life.

2a. Participants randomized to continued use of RehaBot for 10 weeks after treatment (RB) will demonstrate significantly less diminution in accelerometer-based activity counts from post-treatment to 10-week follow-up compared to those for whom RehaBot is withdrawn (No Tx), adjusted for the degree of change in the initial treatment phase.

2b. Participants randomized to RB in the follow-through phase will demonstrate significantly less diminution/ worsening in other outcome domains listed under Hypothesis 1b, compared to No Tx participants.

In addition to testing these hypotheses, we will explore the predictors of treatment response, using pooled data from all participants from pre- to post-treatment. We will analyze in exploratory fashion the predictive effects of demographic and injury characteristics; baseline cognitive, physical, social, emotional, and personality factors; objective and perceived neighborhood characteristics; intrapersonal variables such as motivation, self-efficacy, outcome expectancies, and identity/ values as related to PA; and process variables such as the amount of interaction with RehaBot during treatment.

## Methods

2

### Overview of design

2.1

This is a randomized waitlist-controlled trial, registered prior to participant recruitment at https://www.clinicaltrials.gov (NCT06028334). As shown in Figure 1, after a baseline assessment, participants are randomized 1:1 into IT (10 weeks of GetUp&Go intervention) or WL (10 weeks on waitlist), after which the primary outcome is measured. WL participants then receive 10 weeks of GetUp&Go. The 10-week treatment period (for all participants) is termed the Acquisition or A phase. Directly after the A phase, participants are re-randomized 1:1 into the Follow-Through (FT) phase: 10 additional weeks, of either RB or No Tx. A final outcome assessment and a debriefing interview are conducted at the end of the FT phase.

**Figure 1 F1:**
[figure not shown]
Schematic of trial design showing acquisition (A) and follow-through (FT) phases. BL, baseline; WL, waitlist; IT, immediate treatment; Tx, treatment.

### Participants

2.2

Participants will be 70 persons who meet the following inclusion criteria: (1) age ≥18; (2) TBI (open or closed), sustained at least 6 months prior to enrollment, of at least moderate severity as evidenced by: (a) loss or alteration of consciousness ≥30 min and/ or post-traumatic amnesia (PTA) ≥ 24 h, not due to intoxication/ sedation *and* documented prospectively from the injury (i.e., not retrospectively self-reported); and/ or (b) positive neuroimaging findings consistent with TBI; (3) fully weight bearing on lower limbs and able to walk indoors and outdoors without the assistance of another person (independent use of an assistive device such as a cane is acceptable); (4) cognitively able to participate in treatment, using selected items from the Glasgow Outcome Scale-Extended (49); (5) able to communicate adequately in English for participation in the treatment protocols; (6) informed consent given by participant. Participants are excluded for (1) contraindications to increasing PA as judged by a study physician and/ or study Physical Therapist, using an exam adapted from published screening tools (50); (2) medical or psychiatric instability, including current psychosis or severe uncontrolled substance misuse, as assessed using items from the Mini-International Neuropsychiatric Interview (51), or suicidal ideation with intent or plan, as assessed by the Columbia-Suicide Severity Rating Scale, screening version (52); (3) significant physical or intellectual disability predating the TBI; (4) neurodegenerative disorder, e.g., Parkinson's disease, dementia; (5) insufficiently inactive, i.e., reporting >23 weekly moderate/ vigorous activity units on the Godin Leisure-Time Exercise Questionnaire (53); (6) planned surgery or other hospitalization during the succeeding 9 months; (7) physical or sensory disability (e.g., blindness; severe bimanual incoordination) that prevents use of a smartphone.

### Measures

2.3

The measures collected at each time point are displayed in Table 1. The baseline evaluation (T1) includes psychometric measures and questionnaires as well as demographic and injury-related information collected from medical records and participant interview. Because we have found that primary medical chart information is variable for people with chronic TBI, we measure PTA duration with a structured interview that has been used in other studies and that correlates well with prospectively measured PTA (54). The primary outcome (average activity counts/ minute) and other objective PA outcomes are measured using the wrist-worn Actigraph GT3XP. Activity counts using the GT3XP correlate well with biometric measures of energy expenditure (55). Following a practice prevalent in the PA measurement literature (56, 57), daily activity counts are averaged only from a minimum of 4 full wear days out of each 7-day wear period; if 4 days of data are not recorded, the wear period is repeated or discarded.

**Table 1 T1:** Measures administered at each data collection point.

Type and name of measure	T1	T2/T2b	T3
Demographics: Age, race/ ethnicity, education	X		
Injury severity (estimated days of PTA), time post injury	X		
Episodic memory: Rey Auditory Verbal Learning Test (58) z-scores	X		
Executive function: Trail Making Test (59), Brixton Spatial Anticipation Test (60)	X		
Speed of processing: Symbol Digit Modalities Test (61)	X		
Conscientiousness/ other personality factors: NEO Personality Inventory-Revised (62)	X		
Living situation; use of walking aid; Body Mass Index	X	X	X
Neighborhood characteristics: Safety, walkability	X	X	X
Social support for PA (63, 64)	X	X	X
Type and level of motivation for PA: Exercise Regulations Questionnaire (BREQ-3) (65)	X	X	X
Self-efficacy, outcome expectancies, and identity/ values related to PA (64, 66–68)	X	X	X
Outcome measures			
Accelerometer: average counts/ minute from 4 + days over 7-day wearing period (primary outcome)	X	X	X
Accelerometer: % time sedentary, % time engaged in MVPA, avg daily step count	X	X	X
Self-reported PA: Godin Leisure-Time Exercise Questionnaire (53)	X	X	X
Emotional function: Brief Symptom Inventory-18 (69)	X	X	X
Fatigue: Fatigue Severity Scale, short form (70)	X	X	X
Sleep quality: Pittsburgh Sleep Quality Index (71)	X	X	X
Pain: PROMIS Pain Interference Scale, short form 6b (72)	X	X	X
Health-related quality of life: Quality of Life After Brain Injury (73)	X	X	X

### Procedure

2.4

This study is approved and overseen by an Institutional Review Board (iRISID-2023-1533) and complies in full with the Helsinki Declaration for the protection of human subjects.

Participants are recruited from a variety of sources including two research registries at the study site, as well as clinical programs at the site and others in the geographical vicinity. Recruitment began in December, 2023 and is expected to continue until December, 2026. Prospective participants are screened for eligibility over the phone after expressing interest in the study and assenting to screening. Eligible participants are invited to an in-person session that includes written consent, administration of T1 measures listed in Table 1, and screening by both the study physician and the study Physical Therapist. These screenings include a review of systems and assessment of vital signs, lower extremity range of motion, and mobility. Exercise tolerance is evaluated using the modified Bruce protocol (74). Following the physical/ medical screening and the T1 evaluation, participants are given the Actigraph and instructed to wear it continuously for 7 days as they go about their normal routines in the home and community. Participants are given postage-paid padded envelopes for returning the devices.

After all baseline data including the Actigraph data are collected, participants are randomized 1:1 to IT or WL. Randomization uses a sequence of permuted blocks randomly selected from sizes 6, 9, and 12. The randomization sequence was created by the study statistician and is kept in a securely housed spreadsheet which kept all but the current treatment assignment obscured from view. To maximize equipoise and minimize attrition, participants are informed that the randomization is to “one baseline evaluation” or “two baseline evaluations 10 weeks apart.” WL participants receive periodic contacts from research staff reminding them of their upcoming activities in the program. After this initial 10-week period, the primary outcome is measured with another 7-day Actigraph wear period, followed by telephone administration of the outcome measures listed in Table 1.

When all post-treatment data are collected (at T2 for IT and T2b for WL), participants are re-randomized 1:1 to 10 weeks of RB or No Tx (see Figure 1). T3 data are collected after that interval and as a final step, the participant receives a 15-minute debriefing interview by phone. This interview includes the Patient Global Impression of Change scale (75), worded as follows: “Since your participation in this study, how would you describe the change (if any) in areas of your life that could be related to physical activity and fitness, such as physical and mental well-being, mood, and overall quality of life?” Responses are on a 7-point scale from “No change (or condition has gotten worse)” to “A great deal better and a considerable improvement that has made all the difference.” Other questions are concerned with features of the treatment and the RehaBot app that the participant particularly liked or disliked.

This trial uses masked outcome assessment, with special precautions taken to prevent inadvertent unmasking. These include making treatment information completely inaccessible to data collection staff, and using a “script” reminding participants not to discuss any of their experiences in the program when contacted by a data collector. Any instances of inadvertent unmasking are recorded for later analysis of their influence, and data collectors are asked to guess the participant's treatment allocation following each assessment.

Adverse events (AEs) are documented systematically throughout the trial. AEs are defined as any of the following: 1) Events that initiate the risk management protocol (i.e., expression of suicidal ideation or intent), 2) Events prompting an unscheduled emergency department visit not resulting in hospitalization, 3) Any unanticipated event that is unexpected and related to the study treatment. Serious Adverse Events (SAEs) are defined as outcomes resulting in death, hospitalization, life-threatening circumstances, person at risk of death at the time of the event, disability and/or incapacity, or events requiring intervention to prevent these outcomes. All hospitalizations are considered SAEs, with the exception of planned hospitalizations for elective procedures unrelated to the study intervention. AEs and SAEs are tracked through multiple surveillance mechanisms: spontaneous reporting by participants, discovery by study staff, identification by clinicians during therapy sessions, or detection during study assessments. When an AE is identified or reported, the therapist/data collector completes an Adverse Event Form immediately. This form documents the adverse event type, duration and timing, event details, and resolution status. AEs are reviewed periodically by a Data Safety Monitoring (DSM) team consisting of a physiatrist with extensive experience in msTBI research, and a statistician with expertise in clinical trials methodology. The DSM team also reviews and makes recommendations on recruitment, attrition, and other data relevant to the conduct of the trial and human subjects protections.

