For *Hypothesis 2a*, the primary endpoint is the change in average accelerometer activity counts/ day from post-intervention timepoint (T2 for IT participants, T2b for WL) to the follow-up endpoint, T3, 10 weeks later. The subject-specific T2/T2b-T3 changes will be modeled in an ANCOVA model as dependent on group (RB vs. No Tx) and the average accelerometer activity counts/day during the A phase (from timepoint T1 to post-intervention timepoint T2/T2b). The interaction between group and T1-T2(b) changes will be considered and retained in the model, if significant. If the interaction is not significant, Hypothesis 2a will be tested by comparing the mean change in RB vs. No Tx group using the model-based two-sided two-sample t-test with alpha 0.05. In the case of the main effects model (no significant interaction), this is equivalent to testing the main effect of RB (vs. No Tx) as the difference between intercepts of the regression lines with T1-T2(b) change as a predictor. A significant interaction would imply that the effect of RB (vs. No Tx) depends on the amount of change achieved during the A phase, and the test of interaction corresponds to comparing the slopes of the T1-T2(b) change regression lines between RB and No Tx groups. In the case of a significant interaction, the difference between RB and No Tx groups will be quantified in terms of the difference between the T1-T2(b) change regression slopes, and the significance (*p*-value) for that difference is the same as the significance (*p*-value) of the interaction. It is not expected that this interaction is important, and the study is not powered to detect such interaction. The secondary outcome measures (*Hypothesis 2b)* will be analyzed using the same approach.

We will report AEs and SAEs descriptively by treatment arm, including the number and percentage of participants experiencing at least one AE/SAE, as well as the total number of events by category. All AEs will be categorized by severity, relatedness to the intervention, and resolution status.

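### The H2a/H2b ANCOVA makes no direct adjustment for first-stage arm (IT vs WL), and its A-phase covariate spans different periods in the two arms: a small precision loss, not a bias

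*Protocol article*

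**What the plan says.** Section 2.1 of the article sets out two randomizations. The first is to IT or WL. After the wait, "WL participants then receive 10 weeks of GetUp&Go". Everyone who finishes treatment is then allocated again: "participants are re-randomized 1:1 to 10 weeks of RB or No Tx" (section 2.4; section 2.1 says the same). Only the ratio is given for this second step. The one list scheme described, "Randomization uses a sequence of permuted blocks randomly selected from sizes 6, 9, and 12", follows the sentence on the IT/WL step, and the article does not say whether it covers the second step too.

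Section 2.6 gives the H2a model. Change from T2/T2b to T3 is "modeled in an ANCOVA model as dependent on group (RB vs. No Tx) and the average accelerometer activity counts/day during the A phase", the latter taken "from timepoint T1 to post-intervention timepoint T2/T2b". The rest of that paragraph treats the covariate as T1-T2(b) change, and I read it that way. The interaction of group and covariate is kept if significant. H2b uses the same approach. No IT/WL term appears.

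Section 2.1 defines the phase that the covariate is meant to describe: "The 10-week treatment period (for all participants) is termed the Acquisition or A phase".

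**The concern.** First-stage arm is a factor that the trial itself randomizes, and it is known for every participant at re-randomization. The two kinds of entrant have different histories. WL participants have waited 10 weeks with periodic staff contacts, have completed an extra accelerometer week and interview, and arrive about 10 weeks later.

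If activity after treatment is kept up differently in the two groups, two things follow from leaving arm out of the model. Between-arm variation stays in the error term. Any chance difference in the IT/WL mix of RB and No Tx also passes into the RB estimate without direct adjustment.

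The covariate does not stand in for arm. By the section 2.1 definition it should describe the 10 treatment weeks. As section 2.6 measures it, it starts at T1 for everyone, so for WL it also takes in whatever happened on the waitlist. H2a is planned at only 80% power, so even small avoidable losses deserve a look.

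**Working it through.** **1. The plan's own figure.** Inputs from section 2.6: N = 46 (23 per group), effect 0.85 SD, two-sided alpha 0.05. Noncentrality = 0.85 × √(23 × 23 / 46) = 0.85 × 3.391 = 2.88, with 44 degrees of freedom. Noncentral-t power is 80.5%, against 80% stated, so the figure reproduces. The standard error of the RB contrast is √(2/23) = 0.295, about 0.30 SD.

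**2. Covariate window.** IT: T1 to T2 = 10 weeks, all treatment. WL: T1 to T2b = 10 weeks waiting + 10 weeks treatment = about 20 weeks.

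**3. Chance imbalance if allocation is not stratified by arm.** Assume 23 IT and 23 WL, split into two groups of 23. The number k of IT entrants in RB is hypergeometric, with variance 23 × 0.5 × 0.5 × (23/45) = 2.94 and SD 1.71. The difference in IT share is (2k − 23)/23, with mean 0 and SD 2 × 1.71/23 = 0.149.
- Gap of 20 points or more (k ≤ 9 or k ≥ 14): 24%.
- Gap of 30 points or more (k ≤ 8 or k ≥ 15): 8%.
- Other assumed sizes: with 24 WL among 50, a gap of 20 points or more has probability 16%; with 30 IT and 30 WL, 20%.

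**4. Shift in the estimate.** Shift = gap × arm effect on T2/T2b-T3 change. The article gives no arm effect, so a range is assumed.
- 20-point gap: 0.20 × 0.3 = 0.06 SD; 0.20 × 0.5 = 0.10 SD.
- 30-point gap: 0.30 × 0.3 = 0.09 SD; 0.30 × 0.5 = 0.15 SD.

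The 0.10 SD shift is about a third of the standard error and about 12% of the planned 0.85.

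**5. Effect on the test.** The ANCOVA was simulated with N = 46, unstratified allocation, residual SD 1 and 5,000 runs per setting. Monte Carlo standard error of power is √(0.8 × 0.2/5,000), about 0.6 points. The simulated covariate was unrelated to arm, so the arm effect below is the part that the covariate does not absorb.

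| Assumed arm effect (SD) | Power without IT/WL term | Power with term | Type I error without | Type I error with |
|---|---|---|---|---|
| 0 | 79.5% | 78.5% | 5.1% | 4.9% |
| 0.3 | 79.0% | 78.7% | 4.6% | 4.6% |
| 0.5 | 77.4% | 79.4% | 4.8% | 4.5% |
| 0.8 | 73.1% | 78.2% | 5.2% | 5.4% |

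Without the term, the mean estimate was 0.85 to 0.86 for a true 0.85. With stratified allocation and the term, power was 79% to 80%.

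**The case against.** The strongest reply has four parts.

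- **Allocation.** A 1:1 ratio is compatible with separate lists for IT and WL. The article condenses a fuller protocol, where stratification factors commonly sit. A reader might infer that the second randomization ignores first-stage arm, but the document neither states nor excludes stratification. This part stands in full.
- **Existing adjustment.** A reader might infer that IT/WL differences go wholly uncorrected. They do not: any difference that acts through the change achieved by T2 or T2b is at least partly absorbed by the covariate. This stands in part. For WL the covariate mixes waitlist drift with treatment gain, so it cannot be relied on to carry the arm difference.
- **Validity.** RB vs No Tx is randomized, so an IT/WL imbalance is chance and is already reflected in the standard error. The simulation bears this out. A reading of bias or an invalid test is not supported.
- **Size.** Nothing in the article shows that maintenance differs between IT and WL entrants. Both receive the same program, and H2a is not the primary hypothesis. The loss is negligible unless the arm effect is large. This stands, and it is why the severity is low.

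None of this reaches the model itself. Section 2.6 spells out its terms, so the absence of IT/WL there is stated text, not silence.

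**Conclusion.** The point holds as a low-severity matter of precision. The stated H2a/H2b model leaves out a factor that the trial randomizes and that is known for everyone, and its only covariate measures different periods in the two arms.

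The cost of the omission is nil or not visible at assumed arm effects of 0 to 0.3 SD, about 2 power points at 0.5 SD and about 5 at 0.8 SD. With the term, power stays at about 78% to 79% across that range. These figures rest on N = 46 with equal follow-through groups, 23 entrants from each arm, allocation not stratified by arm, and arm effects that are assumptions throughout. The document supports neither a claim of bias nor a claim that the second allocation disregards arm.

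**What to change.** Pre-specify first-stage arm (IT/WL) as a factor in the H2a and H2b ANCOVA, before analysis. It uses one degree of freedom, costs at most about 1 power point if there is no arm effect, and needs no extra visits or participants. It also covers participants who have already been re-randomized.

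The term takes up the mean difference that the unequal covariate windows create. It does not make the covariate mean the same thing in both arms, so the same edit should reconcile the T1 starting point in section 2.6 with the 10-week definition in section 2.1.

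State whether the second randomization is stratified by IT/WL. If it is not, separate lists for the remaining entrants are an optional second step. With recruitment running from December 2023 to an expected December 2026, they would reach only part of the sample, and the model term matters more.
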